### Economic evaluation

The cost consequences of the TCW-BI and/or chilled water station provision to secondary schools across NSW will be determined. To facilitate this, estimates of intervention effect such as water consumption and the purchasing of SSBs will be calculated at baseline and follow-up. Additionally, all direct and indirect cost estimates relating to the establishment and continuation of the interventions will be collected and assessed from a healthcare perspective. Decision tree modelling, populated by these effect and cost estimates will then be used to estimate the intervention impact in the form of incremental cost-effectiveness ratios (ICERs), accompanied by their respective 95% confidence intervals. Discounting will not be incorporated into the modelling due to follow-up being less than 1 year. One-way sensitivity analyses will be conducted by varying model inputs within a range representing high and low plausible values. Monte Carlo simulation will be used to assess the robustness of our results by varying all model inputs simultaneously over 10,000 iterations in Ersatz (www.epigear.com).

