### Intervention design

The interventions delivered in this study include a behavioural intervention and the installation and promotion of chilled water stations. Following randomisation, schools will be informed of the study arm to which they have been allocated and the project team will work with the school to progress the allocated intervention.

Schools allocated to the behavioural intervention (Arms 1 and 3) will receive health messages regarding SSBs and the promotion of water as a preferred drink through each domain of the Health Promoting Schools Framework (Additional file 1). Within the curriculum, teaching and learning domain students will receive the intervention through the inclusion of messages in year 7 Personal Development, Health and Physical Activity (PDHPE) lessons and through the TCW website which provides a range of relevant resources. Two PDHPE lesson plans and resources pack have been developed in consultation with PDHPE teachers. These lesson plans outline the key water messages as well as a goal based activity for students to decrease their consumption of SSBs and increase their water consumption. To support the implementation of these lesson plans within the PDHPE curriculum professional development opportunities for teaching staff will also be provided.

The school organisation ethos and environment domain will be addressed by messaging through posters, school newsletters, school social media and other opportunities identified locally by schools to engage students and their families (potentially reaching students in other years). The partnerships and services domain will be addressed through a partnership between schools and local immunisation teams, providing an opportunistic avenue for the TCW messages to be further targeted to year 7 students. Post-immunisation students will participate in the Spouts and Straws game (see Additional file 2), trialled in the project pilot. The TCW - BI intervention will occur from July to December, commencing with the curriculum delivery, and with messages being reinforced trough the school organisation ethos and environment domain and then through the immunisation component.

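### ICER confidence intervals may be unbounded or misordered at this trial's precision, and the cost scope conflicts with the stated healthcare perspective

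*Protocol article*

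**What the plan says.** The Economic evaluation section of the protocol article opens with the aim that "The cost consequences of the TCW-BI and/or chilled water station provision to secondary schools across NSW will be determined". It then fixes four things:

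- **Cost scope:** "all direct and indirect cost estimates relating to the establishment and continuation of the interventions".
- **Perspective:** these costs "will be collected and assessed from a healthcare perspective".
- **Result measure:** a decision tree will give the impact "in the form of incremental cost-effectiveness ratios (ICERs), accompanied by their respective 95% confidence intervals".
- **Uncertainty:** one-way sensitivity analyses, and a Monte Carlo simulation "varying all model inputs simultaneously over 10,000 iterations".

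On time horizon it says: "Discounting will not be incorporated into the modelling due to follow-up being less than 1 year".

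Three other sections bear on this. Intervention design places much of the delivery in schools, through curriculum lessons, and adds that "professional development opportunities for teaching staff will also be provided". It also has the stations installed on school sites with water, power and drainage. The Discussion names both the state health service and the state education department as users of the findings. Sample size calculation and Sample give the figures that determine how precisely the effect can be estimated.

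**The concern.** An ICER is a ratio, and its interval behaves well only when the denominator is clearly different from zero. If the trial cannot estimate the effect that precisely, a Fieller interval becomes unbounded. A percentile interval from simulation then mixes two opposite situations. With a positive incremental cost, a draw with negative effect gives a negative ratio. Sorted by size, that ratio ranks below the good draws, although the intervention is dominated in it. The lower limit would then come from the worst outcomes and read as cost saving.

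The second problem is one of meaning. In ordinary health-economic usage, a healthcare perspective leaves out indirect (productivity) costs and costs borne by other sectors. Two analysts following the same sentence could disagree on whether lesson time, teacher development and station running costs belong in the numerator, and so produce different ICERs. The results are meant to inform scale-up by two departments, so the reader must know whose costs were counted.

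**Working it through.** The economic section states no cost, effect or ICER value, so no economic figure can be reproduced. The precision of the denominator can be derived from the sample-size inputs.

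**Inputs.** From Sample size calculation: baseline 40%, 5-point change (so 45%), alpha 5%, power 80%, ICC 0.055, cohort 135, non-response 20%. From Sample: 15 schools per arm. Statistical analysis plan enters the intervention as a four-level variable, which implies single-arm contrasts (15 v 15 schools). The Discussion describes using all schools in both analyses, which implies factorial margins (30 v 30).

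**Reproducing the plan's figures.**
- One-sample formula: (1.96·√0.24 + 0.8416·√0.2475)² / 0.05² = 760.5, so 761 (stated 761).
- Design effect: 1 + 134 × 0.055 = 8.37 (stated 8.37).
- 761 × 8.37 = 6369.6 (stated 6370); 6369.6 / 135 = 47.2, so 48 schools; 48 / 0.8 = 60.

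All agree. This calculation sizes a change from baseline in one group, so it does not guarantee precision for a between-arm effect.

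**Between-arm precision.** Effective n per side = schools × 135 / 8.37. SE = √[(0.24 + 0.2475) / effective n]. The share of draws at or below zero is Φ(−0.05/SE). A Fieller 95% interval is unbounded whenever the estimated effect is within 1.96 SE of zero, whatever the cost data show.

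| Contrast | Effective n per side | SE | 0.05/SE | Draws ≤ 0, centred on 5 points | Fieller unbounded, true effect 5 points |
|---|---|---|---|---|---|
| 15 v 15 schools | 241.9 | 0.045 | 1.11 | 13% | 80% |
| 30 v 30 schools | 483.9 | 0.032 | 1.58 | 6% | 65% |

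With 108 responders per school (20% non-response) the shares at or below zero are 13.6% and 6.0%, nearly the same.

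**What this does to a percentile interval.** Of 10,000 draws, about 1,330 (single arms) or 580 (margins) have no positive effect. The lower 2.5% limit is set by the 250 lowest ratios, so it falls among the negative ones. As an illustration, assume an incremental cost of mean 1 and SD 0.1 in arbitrary units and an effect of mean 0.05, for which the ratio of means is 20. The simulated 95% percentile intervals were:

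- SE 0.0316: −110 to 164
- SE 0.025: 6.8 to 113
- SE 0.018: 11 to 64

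**How much baseline adjustment would be needed.** For an estimate of exactly 5 points, both difficulties recede once SE is below 0.05/1.96 = 0.0255. That is a variance reduction of 1 − (0.0255/0.0317)² ≈ 35% at the margins and 1 − (0.0255/0.0449)² ≈ 68% for single arms. The article gives no figure from which the achievable reduction can be judged.

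**Perspective.** No arithmetic applies. One sentence counts all direct and indirect costs and assesses them from the healthcare side. Intervention design puts lessons, teacher development and station sites in schools. The Discussion addresses the education department. These three statements do not fit together under a healthcare-only perspective.

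**The case against.** The strongest reply has four parts.

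1. ICER intervals are not an error in themselves. Fieller and simulation intervals exist, and a simulation is planned. This stands: the difficulty is conditional on an imprecise effect. But simulation does not remove it, because the draws carry the same uncertainty in the denominator.

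2. The precision figures ignore baseline measures and the planned longitudinal multilevel models, and they concern only the binary water outcome, while the economic section also mentions purchasing of sugary drinks. This stands too. The shares are upper bounds as regards adjustment and say nothing about other effect measures. The water outcome is the only one for which the article gives the inputs.

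3. Indirect may mean overheads, and all costs are to be collected, so omission of school costs is not stated. That is fair. Even on that reading, costs borne by schools lie outside a healthcare perspective, so the mismatch remains.

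4. Net benefit needs a willingness-to-pay value, and none is given. An acceptability curve, or net benefit over a range, needs no single value.

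A reader might also infer that the plan ignores the capital cost of the stations. The text does not support this. Establishment costs are included, and nothing says the purchase is charged in full to one year. Omitting discounting for follow-up under a year is ordinary practice and is a separate choice from annuitisation. How station capital is spread over its life is detail that a full economic plan may supply.

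**Conclusion.** Two points hold. First, the article commits to a ratio interval when, on its own ICC, cohort size and number of schools, the effect may well not be clearly different from zero: unadjusted SE about 0.045 (single arms) or 0.032 (margins), with about 13% or 6% of draws centred on 5 points at or below zero. This rests on a true effect of 5 points from 40%, equal cohorts of 135 and no gain from baseline adjustment. Second, the cost scope and the perspective conflict, and the choice between them changes what the ICER means.

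Two stronger readings should be resisted. One is that the result would be undefined: a Fieller set still exists and percentile limits can still be computed, but they may be unbounded or uninterpretable. The other is that the costing favours the behavioural intervention: leaving out lesson and training time would favour it, leaving out station running costs would favour the stations, and no cost data settle the balance. The issue affects a supporting economic output and leaves the primary effect estimate untouched.

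**What to change.** **Uncertainty.** From the same 10,000 draws, report incremental cost and incremental effect with their own intervals, the cost-effectiveness plane with the share of draws in each quadrant, and an acceptability curve or net benefit over a stated range of willingness-to-pay values. Put these in place of, or alongside, "incremental cost-effectiveness ratios (ICERs), accompanied by their respective 95% confidence intervals". Giving costs and effects separately also suits the section's opening aim. This is a change of wording and output and needs no new effect data. The small downside is that a threshold range must be stated and justified.

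**Perspective.** Choose one of two routes and write it down:
- adopt a health-plus-education perspective, count costs borne by schools, and show healthcare-only as a sensitivity view; or
- restrict the cost scope and the conclusion to the health sector.

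Define indirect costs in either case. The first route may need a short staff-time item in the teacher survey already planned for Arms 1 and 3, and station running costs from Arms 2 and 3. Settle this before delivery, because staff time is hard to recover afterwards.

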## Discussion

Addressing overweight and obesity in adolescents is a significant public health challenge. Whilst a myriad of factors are implicated in addressing this complex issue, the reduction of SSBs consumption and the promotion of water consumption within this population is one emerging approach to address this issue, with school based interventions being increasingly utilised. In the Australian context, however, there is little evidence of this. Of the 36 interventions identified in a recent systematic review of school-base interventions only two were identified as Australian studies and these both focussed more broadly on healthy eating and physical activity interventions, rather than more specifically on SSB consumption [10]. In this context, this current study adds to the evidence, generating new knowledge of how to increase water consumption and decrease SSB consumption amongst adolescents, in an Australian school setting.

The primary aim of the study is to test the effectiveness of number of interventions to increase year 7 secondary student water consumption. These interventions include the delivery of a behavioural intervention delivered within the Health Promoting Schools Framework, the installation of chilled water stations or both. Within the current literature many interventions have a behavioural approach or address the environment, but few studies incorporate both [10], and in reviewing the evidence the provision of both these interventions within one study has not been tested previously in the Australian context or with this age group, and this is a strength of this study.

In addition to filling this evidence gap, there are several strengths to this study. The study design is novel in that it utilises a two by two randomised factorial design, in a real world school setting. To date randomised controlled trials have not been the predominant approach to test interventions regarding SSBs in the school setting. The recent systematic review by Vezina-Im et al. [10] reported only 36% of studies utilised this design. The inclusion use of a factorial design is also beneficial and increases the efficiency of the study by simultaneously investigating two interventions by including all schools in both analyses and to consider both the separate effects of each intervention and the benefits of receiving both interventions together [20]. A further strength of the study design is the testing of the intervention across differing health regions as well as across different secondary settings (including public, private and catholic schools). It is also anticipated that the findings from the study will be robust and generalisable to other school populations, both nationally and internationally, as the inclusion of remote water meter monitoring on chilled water stations will provide an objective, continuous measure of water consumption and will assist to validate the findings from the student self-report survey regarding their water consumption.

This study provides an opportunity to build on a novel approach of using a pre-existing health intervention (the immunisation period) to deliver a choose water message. The provision of both a behavioural component and environmental changes (eg installation of chilled water stations) within the study appears to align well with current evidence that shows the inclusion of both of these approaches produces the most efficacious outcomes in decreasing SSB consumption. It is anticipated that the findings from this study will not only inform NSW Health and the NSW Department of Education of successful scalable interventions, but also contribute to the broader evidence base regarding the health impacts of these interventions in improving water consumption and influencing overweight and obesity in secondary school students.

## Abbreviations

DOB: Date of birth
FOEI: Family occupation and education index
ICERs: Incremental cost-effectiveness ratios
LHDs: Local Health Districts
NSW: New South Wales
PDHPE: Personal development, health and physical activity
SERAP: State education research applications process
SPANS: Schools physical activity and nutrition survey
SSB: Sugar sweetened beverage
SSBs: Sugar sweetened beverages
TCW-BI: *Thirsty? Choose Water!* Behavioural Intervention
US: United States of America
